## Abstract

**Background:**

Studies show that endangered work ability (EWA) can be maintained or restored through medical rehabilitation (MR). For patients, general practitioners (GP) represent an important point of access to MR in outpatient care. However, many different barriers and shortcomings hinder GPs in both timely detection of the need for MR and the recognition of its potentials for their EWA-patients. These are necessary if GPs are to adequately inform patients about MR options and successfully support applications for MR. This study describes the evaluation of a continuing medical education (CME) module designed to improve rehabilitation-related practical performance of GPs regarding a) subjective satisfaction of GPs with the CME module, b) stability of attitudes and knowledge over time regarding rehabilitation, and c) subjective and objective changes in MR-related competencies needed to support MR applications.

**Methods:**

This study is an open, non-randomised, pre-post-intervention study. The intervention involves a CME module for GPs (*n* = 1365) in the German state of Saxony-Anhalt on the topic of medical rehabilitation in connection with the federal German pension fund (Deutsche Rentenversicherung). The module will be initially held as regularly scheduled meetings in moderated GP quality circles (QC), and then offered as a written self-study unit. At the end it will be evaluated by the GPs. The study’s primary focus is on the organizational practice as measured by the number of approved MR applications supported by medical reports submitted by the participating GPs in the 6 months before and 6 months after the CME module. Other study aims involve measuring self-perceived competencies of GPs, as well as their attitudes towards and knowledge of rehabilitation (both upon completing the CME and 6 months later). In addition, the level of satisfaction with the CME module will be analysed among participating GPs and QC moderators (as CME facilitators).

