### Required research

Despite very promising initial evidence from surrogate parameters and secondary data, there is currently little evidence available that points to the effectiveness and efficacy of imparting concrete CME content using the QC format, [27–29].

Evidence is particularly lacking to suggest whether or not controversial topics associated with barriers, such as the MR-related CME content, can be effectively communicated using QC, [23, 27]. For this reason, we see a need, in this study, to evaluate a CME module in terms of improving the rehabilitation-related knowledge and competencies of GPs on the following levels:Subjective GP satisfaction with the CME module,Stability of MR-related attitudes and CME-related knowledge over time, andSubjective and objective changes in CME-related competencies needed to support MR applications.sensitizing for MR as an instrument for prevention

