### Trial design

This study is an open, non-randomised, pre-post-intervention study. Primary and secondary analyses of the data will be undertaken to evaluate the intervention.

Using secondary data from the DRV Mitteldeutschland, responsible for servicing Saxony-Anhalt, the periods of time 6 months before and 6 months after the intervention will be investigated to see how the approval rates change for MR applications made by insured patients for whom the participating GPs have submitted medical reports.

Primary data collection will take place using questionnaires. The satisfaction of the participating physicians with the module will be assessed immediately after completing the continuing education (t1). The influence of the intervention on GP knowledge about and their attitudes towards rehabilitation will be assessed at two different points in time (t0 = immediately prior to the intervention; t2 = 6 months afterwards). The self-rated CME-related competences will be assessed after completing the continuing education (t1) and 6 months afterwards (t2) (Fig. 1).

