### Secondary objectives

To assess how satisfied participants are with the CME module (QC versus independent study)To establish whether or not the CME module improves self-rated skills (QC versus independent study)To determine whether or not completion of the module leads to a gain in knowledge about rehabilitation (QC versus independent study)To investigate whether or not the module positively influences attitudes towards rehabilitation (QC versus independent study)To investigate whether or not the participation of the moderators in the optional informational meeting has an influence on the results

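### Knowledge and attitudes are timed differently in the Abstract and the Trial design, and the apparently operative pre-course and 6-month schedule cannot show retention of what the module taught

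*Protocol article*

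**What the plan says.** The Abstract (Methods paragraph) names the further aims as self-perceived competencies, "as well as their attitudes towards and knowledge of rehabilitation (both upon completing the CME and 6 months later". In the article's notation this is t1 and t2, with no measurement before the course.

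The Trial design section treats the outcomes separately. For knowledge and attitudes: "The influence of the intervention on GP knowledge about and their attitudes towards rehabilitation will be assessed at two different points in time", and these are defined as "t0 = immediately prior to the intervention; t2 = 6 months afterwards". For competences: "The self-rated CME-related competences will be assessed after completing the continuing education (t1) and 6 months afterwards (t2".

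Two kinds of aim rest on these measurements. The Secondary objectives section asks whether completing the module "leads to a gain in knowledge about rehabilitation" and whether it influences attitudes favourably, each with a comparison of QC and independent study. The Required research section names an evaluation level worded as "Stability of MR-related attitudes and CME-related knowledge over time". The same idea appears in the Background paragraph of the Abstract, in Strengths and limitations, and in the Conclusion, which ties it to knowledge that comes from the CME module.

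**The concern.** The two timing statements cannot both be followed. Each is a plain sentence with explicit time points, and no other section reconciles them.

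The second problem is a mismatch between aim and schedule. A gain needs a measurement before the course. Retention of something learned on the course needs one just after it and one later. The Trial design schedule has the first and the last of these three points but not the middle one. If the 6-month score is close to baseline, the investigators could not say whether GPs learned and forgot or did not learn. These findings would point to different remedies: refresher material in one case, a different module in the other. If the 6-month score is above baseline, they could report a net gain but not how much of the initial effect was kept.

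**Working it through.** No sample size, power or error rate is involved. The check is a comparison of the schedules, followed by a short argument about which contrasts each one can estimate.

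**Step 1. Schedules side by side**

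| Outcome | Abstract (Methods paragraph) | Trial design |
|---|---|---|
| Knowledge, attitudes | t1, t2 | t0, t2 |
| Self-rated competences | t1, t2 (parenthesis read as covering the whole list) | t1, t2 |

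The conflict is confined to knowledge and attitudes. The Abstract's timing is the one that the Trial design gives for competences, so the Abstract may have stretched one schedule over all three outcomes.

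**Step 2. Contrasts**

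Let K0, K1 and K2 be the mean score at t0, t1 and t2 in the same GPs.

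- Immediate gain: K1 − K0
- Retention of the post-course level: K2 − K1
- Net 6-month change: K2 − K0 = (K1 − K0) + (K2 − K1)

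| Schedule | K1 − K0 | K2 − K1 | K2 − K0 |
|---|---|---|---|
| t1, t2 (Abstract) | no | yes | no |
| t0, t2 (Trial design) | no | no | yes |
| t0, t1, t2 | yes | yes | yes |

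Under t0/t2 only the sum of the two components is identified.

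**Step 3. Illustration.** The percentages correct are assumed; the article gives none.

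- Learned, then forgot (50, 75, 52): K1 − K0 = 75 − 50 = +25; K2 − K1 = 52 − 75 = −23; K2 − K0 = 52 − 50 = +2.
- Barely learned, nothing lost (50, 52, 52): K1 − K0 = 52 − 50 = +2; K2 − K1 = 52 − 52 = 0; K2 − K0 = 52 − 50 = +2.

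The t0/t2 schedule returns +2 in both cases, although retention differs by 23 points.

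**Step 4. Could t1 data come from elsewhere?**

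- The Intervention section gives the self-study route a final multiple-choice exam that cites the same source as the knowledge outcome in the Outcomes section. Under Data management, completed exams go to the study centre. A post-course knowledge score may therefore exist for self-study.
- No such exam is stated for QC participants, and it does not cover attitudes. It cannot support a comparison of the two formats.
- Data management says that t0 and t1 questionnaires are collected from QC participants but does not give their content. The list of self-study returns names no t0 form explicitly, though one might be included among the evaluation questionnaires.

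**The case against.** The strongest reply is that the article largely shows which schedule governs. The Trial design section is the Methods text and defines its time points. Data management confirms that t0 forms are collected from QC participants, and the Trial design assigns nothing except knowledge and attitudes to t0. The Abstract sentence then looks like a slip of condensation. This stands. A reader might infer from the Abstract that the baseline will be lost, and with it the gain objective; the documents do not support that, at least for the QC route.

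A reader might also infer that a stated objective becomes inestimable whichever schedule is used. That goes too far. The formal list in Secondary objectives asks for a gain and for a favourable influence on attitudes. The t0/t2 schedule estimates both as net change, which is a legitimate target. Stability is not in that list; it belongs to the framing text.

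It can further be said that stability is never defined as t2 minus t1, and that a gain still present at 6 months is a possible reading. This stands in part. The Abstract and Required research speak only of stability over time, but the Conclusion refers to knowledge based on the module, which leans towards retention, and no section adopts the looser meaning.

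Finally, leaving out t1 is defensible because it spares GPs repeated exposure to the same items, and Fig. 1, which is not shown here, may hold more detail. Both are fair. Neither removes the conflict in the text, and the first is a reason to reword the aim rather than leave it as it is.

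**Conclusion.** The concern holds in a limited form. The Abstract and the Trial design contradict each other on when knowledge and attitudes are measured, and the two sections must be reconciled. Taking the Trial design as operative, the two secondary objectives on knowledge and attitudes (of five listed) can be addressed as net 6-month change from baseline. What cannot be addressed is stability in the sense of retention after the module, which is one of the three lettered evaluation levels in the Abstract and the Conclusion.

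The severity is moderate. Only secondary outcomes are affected; the primary outcome, based on pension fund data on applications, does not depend on these questionnaires. The conclusion rests on two assumptions: that the t1 questionnaire does not already carry knowledge and attitude items, as the Trial design implies by naming only two points for them, and that stability means retention of what was learned. If the sponsor intends only that a change from baseline is still visible at 6 months, what remains is a correction of wording.

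**What to change.** In either case, correct the Abstract so that knowledge and attitudes are shown with a t0 measurement, in line with the Trial design. Then choose one of two routes.

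1. **Add t1.** Put the knowledge and attitude items on the t1 questionnaire that already exists, in both formats, and state t0, t1 and t2 in the Abstract and the Trial design. Define gain as t2 minus t0 (with t1 minus t0 as supportive) and stability as t2 minus t1. The cost is a slightly longer form and one more exposure to the same items, which may itself raise later scores.
2. **Keep t0 and t2.** Replace the stability wording with 6-month change from baseline in the Abstract's Background paragraph, Required research and the Conclusion, and for knowledge and attitudes in the matching line of Strengths and limitations. The cost is wording only, and the study gives up any statement about retention.

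Under either route, Data management should say explicitly that self-study participants also return a t0 questionnaire, since the comparison of formats needs a baseline in both. If the module has already been delivered without t1 items, only the second route is open, because a missed post-course measurement cannot be recovered later.

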**Discussion:**

Implementing targeted CME on complex topics such as those involving barriers is possible, even promising, when using QCs and their moderators. Of particular importance is how aware moderating physicians are of the relevance of MR need detection and access.

**Ethics and dissemination:**

The ethics committee of the Martin-Luther-Universität Halle-Wittenberg has registered this study under the number 2014–13. The study will be reported on in peer-reviewed journals and at national and international conferences. The results will be available to current and future initiatives aiming to improve detection of MR need and making MR accessible to EWEC patients needing such support to minimize the effects of chronic disease on their livess.

**Trial registration number:**

German Clinical Trials Register (ID number DRKS00006188) and WHO International Clinical Trials Registry Platform, Universal Trial Number (UTN) U1111–1158-8334.

## Strengths and limitations

Our intervention is important for every participant (QC, postal) and his daily patient treatmentThis study investigates the effect of a CME module focusing on detection of EWA patient needs and access to MR in a pre-post comparison using a large cohort of GPs in the German federal state of Saxony-Anhalt.The evaluation will be done on different levels: subjective satisfaction of the GPs, stability of GP attitudes, knowledge and self-rated competencies regarding rehabilitation over time as well as the objective changes in CME-based competencies as measured in terms of approved MR applications for the participating GPs.We have a self-selection of participants into the two types of interventions, unfortunately we have not a double-blinded randomized study.The self-selection has a significantly influence on results of these interventions.The evaluated CME module uses both the innovative format of the moderated quality circle and the conventional medium of printed materials for independent study, allowing for subgroup analyses of the effectiveness of the two formats.With the accompanying risk of selection bias, recruitment of the GPs permits them to choose between taking the CME module in the QC setting or as independent study.For some participants, there are different starting dates for the pre-post evaluations due to varying meeting schedules for some QCs or as a result of independent study.

## Background

### Endangered work ability and medical rehabilitation

Partaking in gainful employment is essential to individual wellbeing, social involvement and quality of life. In contrast, chronic disease is a significant predictor of a limited ability to practice a profession and/or endangered work ability (EWA) with considerable disadvantages for the individual and society, [1]. Numerous studies demonstrate that EWA due to chronic disease can be maintained or restored through medical rehabilitation (MR) with the goal of returning to work, [2]. Common characteristics can be seen in examples of MR for reasons as diverse as lower back pain, inflammatory arthritis or depression, which are different in their somatic and psychological components: successful interventions restore the balance between individual abilities and workplace demands through changeable factors-either on the level of the individual’s abilities or the demands of the workplace, [3–5]. Medical rehabilitation is an important prevention instrument to inhibit individual increasing chronical diseases. For the individual patient, disease-specific limitations of abilities (e.g. problems concentrating) are, of course, many-sided often requiring complex intervention with many components, for instance patient training, physiotherapy, occupational therapy, psychoeducation and occupational counselling, etc., [2]. Within Germany’s complex administrative system, the most important insurance provider to cover the cost of MR in terms of numbers is the federal German pension fund: the Deutsche Rentenversicherung (DRV). Distinguishing itself through a wide range of in- and out-patient rehab facilities and programs, the DVR is ahead even of the statutory health insurance providers. The applicant for such services and resources is always the individual EWA patient, [6].

### The role of the general practitioner in accessing medical rehabilitation

According to Starfield, coordination of care with other medical care providers is one of the four pillars of primary care, with particular importance for chronically ill patients, [7]. Within this context general practitioners (GP) represent an important point of access to MR in the outpatient setting; primary care physicians are responsible for recognizing need, informing patients about MR programs, supporting applications for rehabilitative medical services across the many sectors of care with well-founded medical reports, and ensuring follow-up care after successful MR. In particular, the medical reports appended to the patient’s application for rehabilitation should contain the pertinent information for evaluation by the insurance provider (in this case the DRV). However, according to social medicine experts these reports often contain insufficient information, [8]. Each year approximately 1,700,000 applications for medical rehabilitation are submitted to the DVR, of these about 1,300,000 are approved. In the course of this, those participating in the process become aware of many barriers in patients, physicians, and the system that stand between an application and its approval, [8–15]:

### Barriers and shortcomings

In a series of surveys, practicing physicians reported substantial problems not only concerning information on detecting the need for MR, the necessary steps patients need to take to apply for MR, and the requirements that supporting medical reports need to fulfil, but also concerning the physicians’ own lack of clarity regarding the criteria for application approval and for asserting objections to rejected applications, [8]. Likewise, the flow of information between the healthcare providers, routine measures within medical practices and, especially, the integration of non-medical health professions into the detection of need for MR and the application process (to relieve the physician workload), all indicate a considerable potential for improvement, [9]. Within other healthcare systems and professional groups similar needs and barriers have also been identified that affect MR case management, [10]. For EWA patients it is the GP’s encouragement and support, alongside psychosocial and family-related factors, that significantly affect a patient’s intention to actively pursue and apply for MR, [11].

It is possible that the main challenge in recognizing the need for MR, and successfully applying for it, can be found in the doctor-patient relationship. Usually, the existence of a potential case of EWA becomes apparent to a GP after a series of episodes during which the patient is unfit for work and seeks a sick-leave certificate, [12]. Qualitative studies show that many practicing physicians see themselves as their patients’ “advocate” and issue the requested medical attestations without further questioning or intervention regarding EWA partly not to jeopardize the doctor-patient relationship, [12]. At the majority of medical practices depressive disorders, for instance, do not merit (pro)-active or EWA-focused approaches as long as other professionals (e.g. psychotherapists) or the patient does not insist on them, [13]. The willingness of GPs to change this situation is rather weak despite the availability of practice- and patient-centred support to relieve workloads, [14].

Patients, in turn, are frequently prevented from forming the intention to pursue and plan for MR because of the negative expectations of their family or social environments, lack of self-efficacy and a (perceived) lack of support, [11]. On top of this, the information about MR compiled specifically for patients is also difficult to understand, [15]. Implementing the strategic goal of pairing eligible patients with the right MR at the right point in time appears to be equally complex, [15].

### Interventions to foster continuing medical education

The number of sick days and incidences of early retirement due to EWA can be reduced by MR (just as by vocational rehabilitation or combinations of the two), [2]. Due to the great social and financial importance of EWA not only for the individuals affected, but also society as a whole, interventions to improve recognition of MR need and access are both imperative and promising, [1, 2].

Approaches to intervention that have been positively evaluated use continuing medical education (CME) to impart knowledge and change physicians’ attitudes, prevention and treatment strategies. There are three different methods to communicate CME content, each of which can be employed separately or in combination:Printed CME materials with little effect on process parameters and questionable effects on patient-centred outcomes and unclear clinical relevance, [16].Audit and feedback on CME with moderate to strong effects—including on patient-centred outcomes particularly if the intervention is repeated among medical colleagues in spoken and written form and covered using a clear agenda, [17].Meetings and workshops on CME can, alone and in combination with other intervention formats, have similar effects as seen with audits and feedback particularly if they focus on topics and outcomes that are considered relevant by the participants, [18].

These formats are used for MR-related CME interventions in current study protocols, frequently in combination or connection with other formats, [19, 20]. A special role is increasingly being played by patient-centred interventions, in which particular risk groups are proactively addressed and/or specially compiled information is presented along with instruments for self-screening, [21, 22].

### Quality circles for CME

Quality circles (QC) are understood to be regular meetings of professionals from the same occupation or interdisciplinary working groups with a defined group of participants, shared goals and professional approaches; leadership is usually taken on by a peer as moderator, [23]. Through moderated interaction with printed or audio-visual materials covering CME content, the QC embodies, in an easily accessible manner, both the format of the meeting/workshop and the elements of audit and feedback through the regularity of the meetings and direct inquiries about individual approaches, [23, 24]. In connection with Germany’s special system of compensation for providing primary care (*Hausarztzentrierte Versorgung,* abbreviated as HzV), QCs as a format for CME (mandatory for HzV physicians) have taken on great importance in recent years, [25, 26].

